## Methods

The trial protocol (V5.0/08.04.19) was granted ethical approval by the North West Greater Manchester South Research Ethics Committee (ref:17/NW/0389). SPIRIT reporting guidelines were used [35].

### Design and Setting

The study was a 12-month pilot 2-arm RCT, performed in patients with T2D and overweight or obesity, recruited from general practices, NHS hospital trusts and an NHS-supported voluntary research register in England. Participants attended trial assessments at Manchester University NHS Foundation Trust (MFT), Manchester, United Kingdom. Participants received dietary support remotely via the Oviva app and/or by telephone.

### Recruitment

Potential eligible participants were recruited from 3 settings using the following methods:

Patients in three general practices in Manchester were sent targeted invite letters and a text message reminder 8 weeks later if there was no response. These practices included a population of patients with T2D ranging from 400 to 700 and reflected different levels of deprivation in England. The England Index of Multiple Deprivation (IMD) score for each practice was 10.9 (least deprived 25% in England) and 29.8 and 44.1 (top 25% deprived in England) [36].Patients at MFT and Stockport NHS Foundation Trust were invited to the study via patient record search and invitation letter, using poster displays, or during face-to-face routine clinical contacts.Patients with T2D (n=2500) on the Help BEAT Diabetes volunteer database (hosted by the National Institute of Health Research Clinical Research Network for Greater Manchester) were contacted via mail or email and asked to check if they met the eligibility criteria for the trial and to contact the MIDDAS trial team if they were interested in taking part.

Those invited by letter had the opportunity to tell the trial team why they did not wish to take part via an anonymous reply slip. Interested patients were invited to an optional group session at MFT to receive more information on the diets and try the Optifast meal replacements before deciding to participate.

The inclusion and exclusion criteria for the trial is detailed in Textbox 1.

Inclusion and exclusion criteria.Inclusion criteriaWilling and able to provide written informed consentMale or female aged between 18 and 75 yearsDiagnosed with type 2 diabetes <8 yearsDiet controlled only or receiving any type of diabetes medications including insulinGlycated hemoglobin (HbA_1c_) ≥48 mmol per mol (6.5%) at baseline (venous blood sample)BMI>27 kg per m^2^ and <50 kg per m^2^ or >25 kg per m^2^ and <50 kg per m^2^ in high-risk ethnic minority groups (ie, South Asian, Black African, and African Caribbean)Access to and ability to use the telephoneWilling to be randomized to an intermittent low-energy diet or continuous low-energy diet using total diet replacement drinksExclusion criteriaRoutine HbA_1c_ ≥108 mmol per mol (12.0%) during the last 3 monthsUnstable retinopathy, grade R2 or higher, or no retinopathy screen within the last 12 monthsPregnant or considering pregnancyPrevious bariatric surgeryCurrent treatment with OrlistatUnintentional weight loss ≥5 kg within last 6 monthsLearning difficulties, lacking capacity or unable to understand EnglishKnown sensitivity to ingredients in the total diet replacementDiagnosed eating disorder. Severe binge eating or very low eating self-efficacy were assessed using the following questionnaires: Binge Eating Scale (BES [37], score ≥27) and Weight Efficacy Lifestyle Questionnaire Short Form (WEL-SF [38], score ≤35)Severe anxiety or depression was assessed using the Generalized Anxiety Disorder Scale (GAD-7 [39], score ≥15) and Patient Health Questionnaire-9 (PHQ-9[40], score ≥15). Hazardous or harmful drinking was indicated by the Alcohol Use Disorders Identification Test (AUDIT [41], score ≥16)Active symptoms associated with emotionally unstable personality disorder, bipolar disorders, psychotic disorders, post-traumatic stress disorder, and current self-harm or suicidal behavior. Participants with these issues were potentially eligible, dependent on further information from their general practitioners and responses to the baseline study questionnairesCurrent treatment with lithium, antipsychotics, or other psychotropic medications that may cause excessive weight gainChronic use of steroidsMedical conditions that in the opinion of the treating physician were at risk of deterioration (eg, severe systemic or organ disease, active cancer, liver, gall bladder disease, and pancreatitis)Current participation in a diabetes drug trial

### Participant Flow and Medication Management

The participant flow through the study is outlined in Figure 1. Informed consent was obtained by the trial research nurse at the baseline appointment. Eligible participants were randomized to ILED or CLED. All participants were invited to attend follow-up appointments at MFT for a repeat of clinical measurements at weeks 8, 12, 28, and 52.

**Figure 1 figure1:**
[figure not shown]
Participant flow through study.

Changes to diabetes and antihypertensive medications specific to each treatment arm are detailed in the trial medication management plan in Table S2 of Multimedia Appendix 1. The CLED medication management protocol was devised by the research team and instructed participants to stop all diabetes medications, with the exception of metformin. Insulin was stopped or reduced, depending on the baseline HbA_1c_ level. Medication management of the ILED arm was adapted from a protocol tested in a recent ILED trial [42]. Medications in both arms were reintroduced or titrated during the trial according to clinical needs. General practitioners (GPs) were notified of the enrollment of patients and changes to their medications by letter.

### Randomization and Blinding

Eligible participants were randomized 1:1 to ILED or CLED by a researcher independent of the intervention using a minimization program stratified by BMI ≥34 or <34 kg per m^2^ (projected mean value from the counterpoint and counterbalance studies [11,12,15]), sex, duration of diabetes <4 years or ≥4 years, and whether participants were prescribed insulin. Due to the nature of the intervention, it was not possible to blind participants and clinicians to the treatment allocation. Clinical assessments were performed by an independent research assistant. Laboratory results were assessed by independent laboratory staff.

### Interventions

Figure 1 shows a summary of the 2 dietary programs. Both included a combination of the Optifast LED and the Mediterranean diet over a period of 12 months. Both programs were designed to have exactly 56 Optifast LED days and an equivalent level of energy restriction during their active weight loss phase and weight maintenance or continued weight loss phase.

#### CLED

##### Active Weight Loss Phase (12 weeks)

Weeks 1 to 8 involved the Optifast LED (Néstle Health Science, United Kingdom). This provided approximately 820 kcal (3430 kJ) per day and consisted of 3 sachets per day of Optifast (200 kcal/837 kJ per sachet of shake or soup made with water) in addition to 8×80 g portions of nonstarchy vegetables (approximately 140 kcal/586 kJ), one dessertspoon of oil per day (80 kcal per 335 kJ), and 2-2.5 liters of calorie-free fluids. The participants were asked to avoid alcohol and excessive caffeine to minimize the risk of dehydration. Participants who were unable to tolerate Optifast were offered a food-based LED with a similar macronutrient profile. This comprised 250 g of lean protein foods (eg, lean meat, fish, eggs, and vegetarian proteins), 5 portions of nonstarchy vegetables, 3 portions of low-fat dairy (eg, 200 ml milk), one portion of unsaturated fat (eg, small handful nuts), one portion of fruit, and one carbohydrate portion (eg, slice of bread). Participants reported their adherence to the LED days throughout the trial during their regular contact with the dietitian.

Diet reintroduction in weeks 9-12 allowed a food-based, energy-restricted Mediterranean diet providing 1000 kcal (4184 kJ) daily in week 1, 1200 kcal (5021 kJ) daily in week 2, 1400 kcal (5858 kJ) daily in week 3, and 1500 kcal (6276 kJ) daily in week 4.

The Mediterranean diet, as described previously by Harvie et al [43], was relatively high in protein (25% energy) with moderate carbohydrate (45% energy from low glycemic load carbohydrates), moderate fat (30% energy from fat: 15% monounsaturated, 8% polyunsaturated, and 7% saturated fatty acids), and limited alcohol to <10 units per week.

##### Weight Maintenance or Continued Weight Loss Phase (40 Weeks)

Participants who achieved a trial weight loss goal of 15%, and/or their target weight if greater, were advised to follow a euenergetic Mediterranean diet for weight maintenance. Those who had not achieved 15% weight loss or wished to lose more weight were asked to follow a 25% energy-restricted Mediterranean diet. Individuals’ estimated energy requirements were calculated using the Mifflin equations [44] to estimate the basal metabolic rate×reported metabolic equivalent of the task. These calculations were based on the revised weight and activity levels after the completion of the active weight loss phase.

#### ILED

##### Active Weight Loss Phase (28 weeks)

The ILED group was asked to include 2 consecutive days per week of the Optifast LED plus 5 days of a Mediterranean diet for 28 weeks. An energy deficit was applied to the Mediterranean diet (up to a value of 265 kcal [1109 kJ] per day) to ensure that the ILED and CLED diets were isocaloric during the active weight loss phase.

##### Weight Maintenance or Continued Weight Loss Phase (24 weeks)

Participants were asked to follow a food-based ILED. Participants who had achieved 15% weight loss, and/or their target weight if greater, were asked to follow the food-based LED described above for one day per week and a euenergetic Mediterranean diet aimed at weight maintenance (eg, 2550 kcal [10,669 kJ] per day for a 50-year-old man, BMI 34) for 6 days. Participants who had not achieved 15% weight loss or wished to lose more weight were asked to follow the food-based LED for 2 consecutive days per week and an energy-restricted Mediterranean diet (eg, 2100 kcal [8786 Kj] per day for a 50-year-old man, BMI 34) for 5 days. This provided an overall daily 25% energy restriction through the week.

#### Relapse

Trial participants who regained 2 kg or more during their weight maintenance or continued weight loss phase were offered one opportunity to resume their initial active weight loss diet to help reverse the weight gain. The CLED group was offered the 820 kcal (3430 kJ) formula Optifast LED for one week, and the ILED group was offered the Optifast LED 2 days per week for 3 to 4 weeks. The relapse program included increased support and monitoring by the trial dietitian and support from the trial psychologist to explore reasons for weight regain and to prevent further relapse.

#### Dietitian and Nurse

The diabetes specialist dietitian provided education on the diets and how to use the Oviva app, either by telephone or face-to-face. All participants were provided with written support materials, including recipes and meal plans. The diabetes specialist nurse provided support for patients who were on diabetes medications other than metformin, on antihypertensives, or who were hypertensive at baseline. All changes to diabetes and antihypertensive medications were agreed upon by the trial doctor and communicated to participants and their GP by a diabetes specialist nurse.

#### Physical Activity

Participants were encouraged to undertake physical activity (PA) throughout the trial to limit the loss of fat-free mass and promote weight loss maintenance. PA was supported by an exercise specialist, and suitability for PA was assessed at baseline using the Physical Activity Readiness Questionnaire (PAR-Q) [45] and signed off by the trial consultant endocrinologist. Participants were encouraged to aim for 5×30 minutes of moderate-intensity cardiovascular PA per week and resistance exercises for the legs, arms, and trunk 3 times per week. They were signposted to local PA services as appropriate and were educated on minimizing the risk of hypoglycemia. Diabetes medications were managed alongside exercise in response to the reported blood glucose readings.

#### Psychological Support

Enhanced psychological support from the trial psychologist was available for participants whose baseline scores indicated moderate scores for binge eating (score 18-26 on BES [37]), self-efficacy (score 36-45 on the Weight Efficacy Lifestyle Questionnaire Short Form (WEL-SF) [38]), anxiety (score 10-14 on the generalized anxiety disorder scale (GAD-7, [39]), depression (score 10-14 on the Patient Health Questionnaire-9 [PHQ-9]; [40]), or risk of alcohol-related problems (score 8-15 on the Alcohol Use Disorders Identification Test [AUDIT]; [41]). Psychological support was also available to participants who relapsed or had been identified by the team as experiencing difficulties impairing their ability to adhere to the programs. Psychological intervention was informed by motivational interviews, cognitive behavioral therapy, behavioral activation, mindfulness, emotional regulation, and distress tolerance skills.

#### Remote Behavioral Support

All participants received regular remote support from a multidisciplinary team including a diabetes specialist dietitian, nurse, and exercise specialist. The frequency and mode of behavioral support are detailed in Tables S1 and S2 in Multimedia Appendix 2. For example, the dietitian contacted the participants weekly via Oviva app messaging in weeks 1 to 12, fortnightly in weeks 13 to 28, and monthly in weeks 29 to 52. Follow-up telephone calls with the dietitian were performed at weeks 8, 12, 28, and 52.

Participants were invited to communicate with the multidisciplinary team via the Oviva app functional on iOS and Android smartphones and tablets. The app facilitates written messages and self-monitoring of diet, weight, blood glucose, weight, and activity levels. Participants were also invited to take part in group messaging on the app with other participants from their allocated diet group. Use of the app was optional, so if participants chose not to use it, then their scheduled contacts were done by telephone.

Participants signed a treatment contract to monitor their blood glucose and BP according to the protocol (Table S1 in Multimedia Appendix 1) and reported these values by telephone or via the Oviva app to the multidisciplinary team. The number of participants in both arms who requested face-to-face dietary consultations during the trial was recorded.

The multidisciplinary team was trained in motivational interview techniques (a well-established model of supporting behavioral change with proven efficacy in facilitating weight loss) to support dietary behavioral changes during both LED programs and in the longer term. Both programs used behavior change techniques such as *problem solving* and *feedback on behavior*, identified in a recent systematic review as being effective in reducing HbA_1c_ [46]. The programs also used established behavior change techniques, such as goal setting and self-monitoring [47].

### Outcomes

#### Primary

Uptake: To achieve an uptake of at least 10% from a primary care mail out.The proportion of subjects in the ILED and CLED groups who successfully lost and maintained >15% weight loss at 12 months, as determined by intention-to-treat (ITT) analysis.The proportion of subjects in both groups who achieved HbA_1c_ <48 mmol per mol (6.5%) at 12 months using ITT analysis.Retention: Aiming for a retention of 60% (48/79) completion as measured by attendance at the 12-month appointment. This is the acceptable completion rate in NICE guidance for commissioning weight management services in England [48].

#### Secondary

##### Process Measures

Participant adherence to the protocol including self-reported adherence to LED days, preference for face-to-face contact with the dietitian, preference for food-based LED days over Optifast, and attendance at follow-up appointments.Download and usage of the Oviva app for self-monitoring.

##### Exploratory Measures

Change in the following measures across the 12-month study period:

Body fat and fat-free mass (bioelectrical impedance)Waist and hip circumferenceBP, lipid profile, and fasting blood glucose levelsNumber and dosage of diabetes and BP medicationsSelf-efficacy for eating, anxiety, depression, and quality of life (as measured by WEL-SF [38], GAD-7 [39], PHQ-9 [40] and Audit of Diabetes-Dependent Quality of Life (ADDQoL) [49] questionnaires, respectively)Quality of diet on non-LED days (as measured by the Mediterranean diet score questionnaire [50])PA (as measured by the Scottish Physical Activity Questionnaire [51])Self-reported satisfaction with weight loss was measured using a 7-point Likert scale. This is highly relevant for the comparison of ILED and CLED, where the CLED will experience faster initial weight loss and achievement of their weight loss goal than the ILED arm [52]Serious adverse events reported up to the end of the 12-month trial

### Measurements

Table 1 provides a summary of the measurements collected at baseline and weeks 8, 12, 28, and 52 by a research nurse.

**Table 1 table1:** Schedule of enrollment and assessments.

Schedule		Enrollment	Follow-up visits			
		Baseline	8 weeks	12 weeks	28 weeks	52 weeks
**Enrollment**						
	Informed consent	✓^a^	—^b^	—	—	—
	Eligibility screen	✓	—	—	—	—
	Randomization	✓	—	—	—	—
**Assessments**						
	Height	✓	—	—	—	—
	Weight	✓	✓	✓	✓	✓
	Waist circumference	✓	✓	✓	✓	✓
	Hip circumference	✓	✓	✓	✓	✓
	Body fat or fat-free mass (impedance)	✓	✓	✓	✓	✓
	Blood Pressure, heart rate^c^	✓	✓	✓	✓	✓
	Blood lipids, liver function, renal profile	✓	—	—	✓	✓
	Fasting plasma glucose	✓	✓	✓	✓	✓
	Laboratory HbA_1c_^d^	✓	—	✓	✓	✓
	Pregnancy urine test	✓	✓	✓	✓	✓
	BES^e^ questionnaire	✓	—	—	✓	✓
	AUDIT^f^ questionnaire	✓	—	—	✓	✓
	WEL-SF^g^ questionnaire	✓	—	—	✓	✓
	PHQ-9^h^ questionnaire	✓	✓	✓	✓	✓
	GAD-7^i^ questionnaire	✓	✓	✓	✓	✓
	EQ-5D-3L^j^ questionnaire	✓	—	—	✓	✓
	ADDQoL^k^ questionnaire	✓	—	—	✓	✓
	Mediterranean diet score	✓	—	✓	✓	✓
	S-PAQ^l^, PAR-Q^m^	✓	—	✓	✓	✓
	Self-satisfaction with the weight loss question^n^	—	✓	✓	✓	✓
	Participant qualitative interviews	—	—	✓ (CLED^o^)	✓ (ILED^p^)	—
	Health care professional qualitative interviews	—	—	—	—	✓

^a^Event or assessment occurred at this time point.

^b^Event or assessment did not occur at this time point.

^c^Further investigation with an ECG if heart rate <50 beats per minute and not on beta-blockers.

^d^HbA_1c_: glycated hemoglobin.

^e^BES: Binge Eating Scale.

^f^AUDIT: Alcohol Use Disorders Identification Test.

^g^WEL-SF: Weight Efficacy Lifestyle Questionnaire Short Form.

^h^PHQ-9: Patient Health Questionnaire scale-9.

^i^GAD-7: Generalized Anxiety Disorder scale-7.

^j^EQ-5D-3L: Measure of health-related quality of life.

^k^ADDQoL: Audit of Diabetes-Dependent Quality of Life.

^l^S-PAQ: Scottish Physical Activity Questionnaire.

^m^PAR-Q: Physical Activity Readiness Questionnaire.

^n^Given the effort you put into following the diet and exercise plan, how satisfied are you with the amount of weight you have lost or gained during the past month? 1=very dissatisfied to 7=very satisfied.

^o^CLED: continuous low-energy diet.

^p^ILED: intermittent low-energy diet.

#### Participant Characteristics

At baseline, we collected information on participants’ age, sex, marital status, number of dependents living at home, ethnicity, education history and employment status, IMD score based on their postal code, relevant medical history, and current medications.

#### Physical Measurements

Weight and body composition were measured using Tanita BC-300MA calibrated scales to the nearest 0.1 kg. Height was measured using a portable stadiometer. Waist circumference was measured halfway between the point of the lowest rib and the iliac crest, and hip circumference was measured at the maximum circumference of the buttocks [53]. All measurements were taken to the nearest 1 mm. BP was measured with patients seated at rest for at least 10 minutes. All assessors were trained in accordance with the departmental protocols.

#### Fasting Blood Sample

A fasting venous blood sample was collected for HbA_1c_, plasma glucose, lipid profile, serum urea and electrolytes, eGFR, creatinine, and liver function tests. A urine pregnancy test was performed in women of childbearing age to exclude pregnancy. Pregnant women were excluded from the trial. Laboratory results were assessed by independent laboratory staff.

#### Questionnaires

The full list of questionnaires referenced in Table 1 is BES [37], WEL-SF [38], GAD-7 [39], PHQ-9 [40], AUDIT [41], PAR-Q [45], ADDQoL [49], Mediterranean diet score [50], Scottish Physical Activity Questionnaire [51], and EQ-5D-3L [54] (standardized validated instrument used to measure general health status). All questionnaires for which a third party does not own the copyright can be found in Multimedia Appendices 3 [37], 4 [38], 5 [39], 6 [40], 7 [41], 8 [45], 9 [50], 10 [51], and 11 [54].

### Retention and Withdrawal

Participants had the right to withdraw from the trial at any time. Participants were considered as withdrawn from the trial if they withdrew from the study intervention voluntarily or if they failed to return for follow-up assessments. Participants could also be removed by the principal investigator if this was considered necessary for medical reasons or due to ineligibility arising during the study (eg, pregnancy). Reasons for withdrawal were recorded, and their GP was notified with recommendations for follow-up care where appropriate. Participants who withdrew continued to have weight and HbA_1c_ collected from their routine diabetes clinic or GP visits for the duration of the 12-month trial unless they did not consent to this at baseline. No incentives were provided to the participants to promote retention and follow-up.

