### Sample Size and Statistical Analysis

The total number of participants recruited for the study was 79. The sample size was selected to allow an estimate of uptake within ±6.6% of the target uptake of 10% [55] with 95% confidence while allowing the research team to obtain sufficient data on the feasibility and potential efficacy of the ILED and CLED.

This study will not undertake significance tests of changes to the primary outcome measures. Descriptive, graphical (summary), and basic inferential statistics of outcomes will be presented as appropriate, for example, frequencies and percentages, mean and SD, or median and quartiles. Confidence intervals (95%) will be calculated to show the change from baseline in the outcomes for each group.

Questionnaires used as outcome measures are quantitative and will be analyzed using appropriate descriptive statistics as per standard.

Changes to diabetes medication will be presented using the medication effect score (MES). The MES for a participant is the sum of the MES for each of their individual medications, where MES=actual drug dose/maximum drug dose×drug mean adjustment factor. A decrease in MES corresponds to a decrease in the use of diabetes medications [56]. Changes to BP medications will be presented using a Treatment Intensity Score (TIS) defined as the actual drug dose/maximum drug dose [57]. The TIS for a participant is the sum of the TIS for each of their medications, and a decrease in TIS indicates a decrease in BP medications.

An ITT analysis using multiple imputations will conducted for percentage weight loss, HbA_1c_, and MES. All other outcomes will be presented only for those who completed the trial.

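### Open-ended removal of randomised participants, combined with completers-only reporting, allows post-randomisation selection in the questionnaire outcomes

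*Protocol article*

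**What the plan says.** All references are to the protocol article.

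- **Retention and Withdrawal.** Withdrawn participants are those who stop the intervention by choice or do not return for assessments. In addition, participants could be "removed by the principal investigator if this was considered necessary for medical reasons or due to ineligibility arising during the study"; pregnancy follows as an example. Reasons are recorded. Weight and HbA1c continue to be collected from routine care for those who withdrew, subject to consent at baseline.
- **Recruitment, Textbox 1.** Exclusion limits include "Severe anxiety or depression was assessed using the Generalized Anxiety Disorder Scale (GAD-7 [39], score ≥15) and Patient Health Questionnaire-9 (PHQ-9[40], score ≥15" and "Weight Efficacy Lifestyle Questionnaire Short Form (WEL-SF [38], score ≤35".
- **Outcomes, Exploratory Measures, and Table 1.** PHQ-9, GAD-7 and WEL-SF are outcomes and are measured again during follow-up.
- **Sample Size and Statistical Analysis.** Percentage weight loss, HbA1c and medication effect score (MES) are analysed by intention-to-treat with multiple imputation. For the rest: "All other outcomes will be presented only for those who completed the trial".
- **Randomization and Blinding.** The article states that "it was not possible to blind participants and clinicians to the treatment allocation".

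**The concern.** Medical necessity is already a ground for removal, so ineligibility that develops later is a second and wider one. It has one example and no closed list. Some of the criteria that define eligibility are the same scales on which the diets are judged for psychological effect. A participant whose mood or eating self-efficacy worsens after randomisation can come to meet an exclusion criterion through the outcome itself.

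If such a participant were removed, the completers-only rule would take all their questionnaire data out of the report, including the visits they attended. That is selection on a post-randomisation value, at the discretion of someone who probably knows the allocation. At stake is whether the questionnaire summaries describe the people who were randomised. The outcomes are exploratory, but the pilot is meant to inform whether and how a full trial proceeds.

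**Working it through.** The plan gives no figure for this point, so the check is to set its statements against one another and then illustrate the scale.

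**1. Which entry limits are also reported outcomes?**

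| Scale | Entry exclusion | Repeated at weeks | Listed outcome? | Analysis set |
|---|---|---|---|---|
| PHQ-9 | ≥15 | 8, 12, 28, 52 | Yes | Completers |
| GAD-7 | ≥15 | 8, 12, 28, 52 | Yes | Completers |
| WEL-SF | ≤35 | 28, 52 | Yes | Completers |
| BES | ≥27 | 28, 52 | No | – |
| AUDIT | ≥16 | 28, 52 | No | – |
| HbA1c (upper limit) | ≥108 mmol/mol, routine value in the 3 months before entry | 12, 28, 52 (laboratory) | HbA1c is an outcome | Intention-to-treat, imputed |

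The overlap that matters is PHQ-9, GAD-7 and WEL-SF. A limit can be crossed before the last visit at weeks 8, 12 or 28 for the first two, and only at week 28 for WEL-SF.

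**2. What happens to a removed participant's data?**

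- Questionnaires: not a completer, so not shown, even for visits attended.
- Weight and HbA1c: counted among the 79. Routine-care collection is worded for those who withdrew, and removal is described in a separate sentence, so its cover of removed participants is implied rather than stated.
- MES: counted among the 79, but no collection after withdrawal is stated, so it would rest on imputation.
- Retention: judged by attendance at 12 months. The target is 60%; 0.60 × 79 = 47.4, so 48 attenders, which leaves room for 79 − 48 = 31 non-attenders. A removed participant who does not attend counts against it.

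**3. Who decides?** Clinicians are unblinded. The principal investigator's status is not given separately, but the Trial Steering Committee and Trial Management Group section places the principal and chief investigators on the groups that review safety and adverse events. Knowledge of the arm is likely, though not stated. "Clinical assessments were performed by an independent research assistant" protects measurement, not the removal decision.

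**4. Illustration of scale (assumed inputs).** The document gives neither a score distribution nor a removal count. Suppose everyone with PHQ-9 ≥15 at a visit before week 52 were removed, and scores were roughly normal with mean m and SD s. With a = (15 − m)/s, the share removed is 1 − Φ(a), and the mean of those left is m − s·φ(a)/Φ(a).

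| m, s | a | Share removed | Of 79 | Shift in mean |
|---|---|---|---|---|
| 5, 4 | 2.5 | 0.6% | 0.5 | −0.07 |
| 6, 5 | 1.8 | 3.6% | 2.8 | −0.41 |
| 8, 5 | 1.4 | 8.1% | 6.4 | −0.81 |

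Within one arm of 40, if k are removed and each scores d points above the rest, the arm mean falls by k·d/40. For k = 1 and d = 8 this is 0.2; for k = 4 and d = 12 it is 1.2. The share at ≥15 for that visit would read 0% instead of 1/40 = 2.5% to 4/40 = 10%.

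These figures describe the summary of the visit at which the limit was crossed, and they assume removal of everyone over it. They show what the wording allows, not what happened.

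**The case against.** The strongest reply is that nothing in the article makes a follow-up score a trigger for removal. The only example is pregnancy, and for participants in difficulty the Psychological Support section offers support, not removal. If every entry criterion kept applying, falling below HbA1c 48 mmol/mol or to a BMI of 27 would also make a participant ineligible, yet HbA1c below 48 is a primary success outcome. The article also condenses a fuller protocol, which may define the ground more tightly. And completers-only reporting affects every dropout, not just those removed.

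Most of this stands, and it rules out several stronger readings that a reader might infer:

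- *The worst scorers are removed.* The text allows this but does not require it, and read literally it could also remove successes. The direction is open.
- *The primary weight and HbA1c results are compromised, or the rule contradicts intention-to-treat.* Leaving the trial is not exclusion from analysis; all 79 stay in, and routine-care collection most naturally covers removed participants too. The upper HbA1c limit is a screening look-back and is not shown to apply to trial samples.
- *No completer could have a severe score.* Someone first crossing a limit at week 52 has attended the final visit and is reported.
- *Removal would differ by arm because the medication plans differ.* Nothing links those plans to eligibility.

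What the reply does not remove is the combination. The article states an open-ended, discretionary ground for removal and separately fixes an analysis set from which anyone removed disappears. Unlike ordinary dropout, this is a decision made by trial staff.

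**Conclusion.** The point holds in a limited form. The wording permits removal of randomised participants on grounds that can coincide with PHQ-9, GAD-7 and WEL-SF outcomes, and completers-only reporting would take their questionnaire data out of the results. The consequence is confined to exploratory outcomes in a pilot that plans no significance tests of its primary outcomes. For weight and HbA1c, the remaining gap is one of wording: follow-up of removed participants should be stated. If removal did depend on outcome, imputing from those who remain could also be optimistic.

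Neither size nor direction can be given, because the article reports no removals. The illustrated shifts of 0.07 to 0.81 points over 79, or 0.2 to 1.2 points within an arm, rest entirely on assumed scores and on removal of everyone over the limit. If nobody was removed on this ground, there is no effect, and a short listing would show that.

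**What to change.** 1. State that ineligibility arising after randomisation may lead to the diet being stopped but does not end trial follow-up or membership of the analysis. Striking the ground out altogether is less well aimed: it would also drop the pregnancy example and sit badly with the Fasting Blood Sample section, which says that pregnant women were excluded from the trial. Those two places need to be reconciled.
2. State that removed participants, like those who withdrew, continue to have weight and HbA1c collected from routine care, subject to the same consent.
3. Present PHQ-9, GAD-7 and WEL-SF at each visit for all randomised participants with available data, alongside the completers.
4. List any removals by arm, with the reason and the last recorded values, or state that there were none.

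Data collection ended in February 2020, so items 3 and 4 are what can still change this trial's report. Both use data already held, since reasons for withdrawal were recorded. Items 1 and 2 clarify the analysis of this trial and the wording for any full trial. The cost is a few sentences, one extra set of descriptive tables and a short listing. Clinical decisions on stopping the diet are not changed.
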